### Postnatal follow-up procedures

Women participating in the control arm of the trial who have a positive urine STI test result during antenatal follow-up will be provided with appropriate treatment by the study team at the first postnatal visit. Procedures for postnatal follow-up visits will otherwise be the same in each trial arm. Eye and nasopharyngeal swabs will be collected from a sub-set of up to 2000 newborns in five randomly selected trial clusters to address secondary objectives 7–9.

*First postnatal follow-up visit (within 72 hours; all participants)*

○ A first postnatal follow-up visit will be conducted by the trial team as soon as possible after birth to collect primary outcome data (birth weight, date and time of birth); and clinical information, including adverse maternal and newborn health outcomes. Data will be recorded in study-specific CRFs at the time the measurements and interview are conducted. A summary of key findings will also be recorded in the participant’s client-held Health Record Book.

○ Participants who give birth at a health facility will be visited at the facility by a research nurse/midwife. Those who give birth in the community will be visited at home by a study community nurse/midwife.

○ The trial team will aim to conduct all first postnatal visits within 72 hours of birth. Baby weight measured in postnatal visits conducted more the 72 hours but less than 1 week after birth will be categorised as ‘late birth weight’ and will not contribute to the primary outcome.

○ Birth weight data recorded by labour ward staff in client-held Health Record Books at the time of childbirth will be captured at postnatal visits conducted by the study team. If the study team have been unable to conduct a postnatal visit within 72 hours of birth, the birth weight as recorded in the client-held record book will be used in statistical analyses and contribute to the primary outcome of the trial. All health facilities participating in the trial (and other local facilities where study participants may give birth, such as provincial hospitals) will be provided with medical grade infant weighing scales accurate to within 10 g. Scales used by the study team and those at local health facilities will be calibrated monthly in accordance with study-specific standard operating procedures (SOPs).

○ Adverse maternal and/or neonatal health outcomes will be treated in the community and/or referred to local health services as indicated, in accordance with PNG national guidelines.

In clusters randomised to take part in the extended neonatal component of the trial, two eye swabs (one from each eye) will be collected from babies at this visit (for comparison of GeneXpert CT/NG Test and a laboratory-based NAAT platform)

*Second postnatal visit (1–2 weeks; sub-set of 2000 participants only)*

○ A second postnatal visit will be carried out in the participant’s home to collect information on adverse maternal and newborn health outcomes (including neonatal eye and respiratory symptoms) and health service utilisation.

○ A neonatal examination will be conducted and baby weight measured as above. Adverse maternal and/or neonatal health outcomes will be treated in the community and/or referred to local health services as indicated, in accordance with PNG national guidelines.

○ The following specimens will be collected at this visit:

•Two eye swabs from neonates with any clinical signs of conjunctivitis and from a random 15% sample of neonates with no clinical signs of conjunctivitis (one for GeneXpert CT/NG Test, and one for storage and later testing using a laboratory-based PCR platform)•Two nasopharyngeal swabs (one for Xpert CT/NG Test, and one for storage and later testing using a laboratory-based PCR platform)

○ Neonates with a positive test result will be followed-up in the community and provided with appropriate antibiotic treatment in accordance with PNG national guidelines.

○ Data collected during the visit (and any treatment provided and/or referral initiated) will be recorded in study-specific CRFs at the time of the visit. A summary of key findings will also be recorded in the participant’s Health Record Book.

*Third postnatal visit (4–6 weeks; sub-set of 2000 participants only)*

○ A third postnatal visit will be conducted home to collect information on adverse maternal and newborn health outcomes (including neonatal eye and respiratory symptoms) and health service utilisation. Visits will be conducted at participating health facilities when mothers and their babies attend for routine infant diphtheria-tetanus-polio (DTP) vaccination, or at home if participants miss a routine vaccination clinic.

○ Data will be extracted from client-held health record books and health facility records of investigations, diagnoses and treatment where available.

○ Procedures for the collection of health information, and treatment provided will be the same as at the second postnatal visit, described above.

○ The following specimens will be collected at this visit:

•Two nasopharyngeal swabs (one for Xpert CT/NG Test, and one for storage and later testing using a laboratory-based PCR platform).•Eye swabs will not be collected unless clinically indicated at this visit.

○ Infants with a positive test result will be followed-up in the community and provided with appropriate antibiotic treatment in accordance with PNG national guidelines.

### Collection of economic evaluation data

The cost effectiveness analysis will be performed according to the intention-to-treat principle and from a health service and societal perspective. It will measure and value the resource use of providers and participants. This includes all costs of the intervention, including local health service implementation net costs (such as the costs of service provision, medicines, diagnostic tests, changes to staff time, other aspects of workflow, and supervision, adjusting for any user fees observed); participant out-of-pocket costs (such as transport, accommodation); and costs of production losses (such as participant’s and family’s time-off work or normal activities). The project costs of delivering the intervention will be collected retrospectively from the project accounts and entered into a standardised data capture tool designed for this purpose following standard practice
^64^. Costs incurred by health care providers (i.e. participating health facilities) will be collected prospectively from health service records (below) that capture data on changes in service provision, patient flow, staff allocation of time, and resource use (drugs and equipment); combined with available financial data on the average unit cost of delivering the services in both arms of the trial
^65^. Participant costs will be assessed prospectively using a context-specific client CRF covering cost of care-seeking that will be administered by research staff to all participants at enrolment, at antenatal follow-up visits and postnatally. This CRF will also include questions to assess client acceptability of the intervention (see below). The health economics research component of the trial will be described in detail in a separate protocol paper.

### Collection of health system implementation data

All trial facilities will be assessed at baseline and up to twice during implementation to collect health service data through examination of facility records, observation of facility procedures, and semi-structured interviews (SSIs). SSIs will collect provider costs (capital and recurrent) and other health service feasibility and acceptability data, including changes in service provision, patient flow, staff allocation of time, and resource use (drugs and equipment). SSIs will be conducted with members of the in-country clinical research team (1–3 staff per cluster; 10–30 interviews in total); clinic staff in participating antenatal clinics (1–3 staff per facility; 10–30 interviews in total); and health managers at district, provincial, national level (10–15 interviews in total). Health care managers and providers being interviewed or observed will complete separate informed consent procedures, and interviews digitally recorded with participants’ consent. Interview topics will include:

○ Rapid health system screen for changes in antenatal service delivery, facility staffing, health information, financing and payments, clinical governance, and community/patient engagement.

○ Staff workflow and patient flow specific to the conduct of point-of-care STI testing, counselling and treatment.

○ Provider views on training requirements, confidence in test results obtained, experiences of providing results to participants.

○ Provider views on resources needed in terms of capital and recurrent costs to health service and clients, staffing and infrastructure.

○ Provider views on changes in client attitudes to and utilization of antenatal services, including frequency and timeliness.

○ Opinions on enablers of and barriers to deployment of antenatal point-of-care STI testing in general and GeneXpert-based point-of-care testing in particular.

An observational assessment and an examination of facility records will also be conducted at the time facilities are visited for SSIs. The observational assessment comprises a structured observation of clinic processes, and will include quantification of staff work-flow and patient-flow. Observational assessments will be conducted at baseline, and at early and late time points during trial implementation at clinical sites. The examination of facility records will review clinic activity levels relevant to the study including staff time and other resource allocations, utilisation patterns, timeliness of antenatal care, clinical complications of pregnancy and timing of diagnosis and treatment. The health systems research component of the trial will be described in detail in a separate protocol paper.

### Collection of acceptability data

Client acceptability of the intervention, and accompanying service changes, will be measured in two ways. First, questions embedded in the CRF on cost of care-seeking (see above) will be administered by research staff to all participants at enrolment, and antenatal and postnatal follow-up visits. These data will be supplemented by SSIs (coordinated with the SSIs conducted above) in a subset of up to 200 women, enabling qualitative triangulation of issues raised in other data collection activities. Interviews will be administered by research staff trained in culturally sensitive collection of qualitative information. Due to the iterative, validating role of these SSIs, their structure and themes will be revised (within the confines of the outline interview guide approved by research ethics committees) based on early findings from acceptability CRFs and provider interviews.

### Adverse events and safety reporting

***Reporting framework.*** Adverse Events (AEs) occurring during the course of the trial will be monitored, managed and reported in accordance with guidance from the UK Medical Research Council, and the UK National Health Service Health Research Authority, in particular their guidance on safety reporting in human research trials that are not clinical trials involving investigational medicinal products (non-CTIMP trials:
https://www.hra.nhs.uk/approvals-amendments/managing-your-approval/safety-reporting/). The WANTAIM trial is evaluating the use of established STI diagnostic assays and providing the same antibiotics for the treatment of infections as currently used for STI syndromic management in PNG. No new investigational medicinal products are being evaluated in the trial.

***Protocol definition of Serious Adverse Event.*** The protocol definition of a serious adverse event (SAE) is based on UK guidance for non-CTIMPs trials (
Box 1). This definition is consistent with ICH GCP and current MRC UK guidelines. All SAEs as defined will be reported within 72 hours of the Trial Coordinator and/or Chief Investigator becoming aware of the event.

Box 1. Protocol definition of serious adverse event.
**In research other than CTIMPs, a serious adverse event (SAE) is defined as an untoward occurrence that:**
(a) results in death;(b) is life-threatening;(c) requires hospitalisation or prolongation of existing hospitalisation;(d) results in persistent or significant disability or incapacity;(e) consists of a congenital anomaly or birth defect; or(f) is otherwise considered
medically significant by the investigator.**
**An SAE occurring to a research participant should be reported to the main Research Ethics Committee where in the opinion of the Chief Investigator (CI) the event was:**

Related – that is, it resulted from administration of any of the research procedures, and
Unexpected – that is, the type of event is not listed in the protocol as an expected occurrence.** In the WANTAIM trial, the following conditions will be considered
medically significant and categorized as SAEs:spontaneous abortion / miscarriagestillbirthearly neonatal deathdomestic violence resulting in injury that requires medical attention

### Sample size

Sample size requirements were based on our earlier findings about the incidence of the primary outcome in PNG
^13–
15,
66^. The proportions of pregnancy resulting in preterm birth and low birth weight were estimated to be 15% each, and 18% combined. Research findings on the relationship between STIs and birth outcomes suggest that effective STI treatment could reduce this combined proportion by up to 45%
^27,
33^ in those with STIs. This reduction would translate into a relative reduction of around 23% in a population in which nearly half of all pregnant women have chlamydia, gonorrhoea, trichomonas and/or bacterial vaginosis, as is the case in PNG
^14^. To measure this effect size with α=0.05, β=0.20 (80% power), and an estimated intra-cluster correlation coefficient (ICC) of 0.003, 16 clusters of 200 women would be required in a cluster randomised crossover trial (8 clusters per phase; 3200 women in total). In case one or more trial cluster does not successfully complete the trial, two additional clusters will be added (10 clusters of 200 women in each phase; 4000 women in total). Based on our earlier work in this setting
^66–
68^, we anticipate loss to follow-up for the primary outcome of around 10–15%, so we will recruit a total of 4600 women from 10 clusters in two phases (230 women per cluster in each phase of the trial).

### Methods for minimising bias

To minimise the risk of selection bias due to differences in the proportion of eligible women enrolled in larger compared to smaller clinical centres:

○Human resource allocation, equipment, consumables and logistics support will be increased in clusters having the highest weekly attendance figures to facilitate optimal participant accrual across all sites.○Site-level accrual will be monitored weekly by the Trial Coordinator and presented at quarterly Trial Management Group (TMG) meetings held throughout the course of the trial. The total number of women attending their first antenatal clinic visit, total enrolled, total excluded, and total who declined to join the study, will be recorded in a weekly tally sheet at each site.

Attrition bias in the ascertainment of outcomes will be minimised by the use of previously tested strategies for ensuring high levels of follow up. To minimise performance bias we will be using the same procedures for routine antenatal care in all clinics. Detection bias will be minimised by assessing outcomes as objectively as possible and by blinding assessments wherever possible.

### Statistical analysis

The statistical analysis plan for the trial will be presented in detail in a separate manuscript.

All analyses (including the cost-effectiveness analysis) will be conducted using methods that take into account the cluster-randomised cross-over design. All analyses will be carried out using the latest available version of Stata statistical software (15.0 or above; College Station, TX, USA).

Primary data analysis will be by intention to treat (ITT) at the cluster level, meaning that all participants with a recorded outcome will be included in the analysis, and will be analysed according to the treatment group to which they were randomised; and all clusters will be included in the analysis according to the treatment group to which they were randomised. Initial analyses will be unadjusted comparisons of intervention and control clusters. If there appear to be any important imbalances between randomised groups in terms of baseline demographic characteristics, risk factors for low birth weight and/or preterm birth, and the prevalence of specific STIs, adjusted analyses will be performed, and presented in addition to unadjusted comparisons.

Effect measures, comparing outcomes between intervention and control clusters, will be estimated with 95% confidence intervals and p-values from the corresponding hypothesis tests. The effect measure for the primary outcome will be a risk ratio, defined as the ratio between the proportion recorded as having the outcome of interest in the intervention arm, and the corresponding proportion in the control arm.

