### Enrolment visit procedures

Women attending routine antenatal clinics in both the control and intervention arms of the trial will receive standard antenatal care in accordance with PNG national guidelines
^59^. All women will be advised to return for a minimum of three additional antenatal clinic visits, in accordance with national and WHO recommendations; and to attend a health facility to give birth.

*Procedures at enrolment: control clusters*

a) The following routine antenatal clinic procedures will be conducted
^59^:

○ A face-to-face clinical interview conducted in the most appropriate language (e.g. English or PNG Pidgin) to collect baseline antenatal data, including current and past obstetric history.

○ A general medical and obstetric examination, in which the following will be recorded: general health and well-being; signs of anaemia or other systemic disease (e.g. tuberculosis); weight and height; blood pressure; fundal height and foetal heart rate.

○ Provider initiated counselling and testing for HIV (PICT) and syphilis infection, as per PNG national guidelines.

○ Collection of specimens for routine on-site testing: haemoglobin (Hb) estimation; rapid diagnostic test (RDT) for malaria (if symptomatic e.g. fever); collection of a midstream urine specimen for urinalysis (protein and glucose testing).

○ Women will be provided with routine antenatal care as per PNG national guidelines, including sulphadoxine-pyrimethamine for malaria prevention; iron and folate supplementation; tetanus toxoid immunization; treatment for syphilis if required; and STI syndromic management for women presenting with genital symptoms, as per PNG national guidelines.

○ Women with a positive RDT for malaria will be given malaria treatment in accordance with PNG national treatment guidelines.

○ Women who test positive for HIV infection will be referred for specialist review and initiation of antiretroviral therapy.

b) The following study-specific procedures will be conducted:

○ Collection of additional clinical, behavioural and socio-economic and demographic information, including risk factors for low birth weight and preterm birth (e.g. smoking, alcohol and betel nut consumption; recent or current systemic illness, e.g. malaria or tuberculosis; poor maternal nutritional status, e.g. mid-upper arm circumference <22 cm)
^61–
63^

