○ A trans-abdominal obstetric ultrasound examination to measure biparietal diameter (BPD), head circumference (HC), femoral length (FL) and abdominal circumference (AC), to estimate gestational age, as specified in study-specific standard operating procedures.

○ Storage of residual urine specimen for off-site STI PCR testing to be conducted in batches in order to obtain information on the prevalence of curable STIs (
*C. trachomatis, N. gonorrhoeae, T. vaginalis* and bacterial vaginosis) among women participating in the control arm. Urine remaining after off-site STI testing will be retained for future laboratory testing with participants’ written consent.

○ Women with a positive urine test result will be counselled regarding their diagnosis and provided with treatment for them and their partner at the first postnatal visit conducted within 72 hours of birth.

○ A dried blood spot (DBS) will be collected and stored for later off-site malaria quantitative real-time PCR (qPCR) testing.

○ Information will be recorded in a study-specific Enrolment Case Report Form (CRF) at the time the measurements and interview are conducted.

○ A summary of key clinical findings will also be recorded in the participant’s Health Record Book that will be checked to see if any visits to a health centre have been documented. If the participant has any record of such a visit, the field study team will record the date of the most recent visit and any medication the participant received in the Enrolment CRF.

○ At the end of the Enrolment visit, a short interview with a dedicated community volunteer will be conducted in order to collect home address and other locator information to facilitate future community tracing and postnatal follow-up. A separate Locator Form will be used to record this information and will be securely stored in a different location to completed Enrolment CRFs.

*Procedures at enrolment: intervention clusters*

Enrolment procedures in intervention clusters will be identical to those in control clusters, with the following exceptions:

○ Women will provide two self-collected vaginal swabs for same-day, point-of-care testing at the study health centre:

a) one swab will be tested for chlamydia, gonorrhoea and trichomonas using the GeneXpert platform; andb) one swab will be tesed for bacterial vaginosis, using the BVBlue Test.

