○ Clinic staff will use a laminated pictorial guide to help them explain the correct way to collect vaginal specimens for STI testing. During the explanation, staff will indicate how samples are to be collected using a specimen collection kit reserved for this purpose, and will encourage women to handle the swabs and to review the pictorial guide themselves.

○ When staff are satisfied that the participant understands the collection procedure, she will be asked to collect her specimens in a private room or the clinic toilet. This approach has been successfully used in our earlier research and found to be acceptable to both study participants and clinic staff.

○ Women who have a positive STI test result will be provided with immediate, directly observed treatment in accordance with PNG national guidelines for the management of STIs. Women will also be counselled regarding the importance of providing STI treatment for their husband/partner in order to prevent re-infection, and the most appropriate options for ensuring successful partner treatment (e.g. same-day treatment if accompanied by their partner; provision of a partner treatment pack; return for couple counselling and treatment).

○ Only those with a positive STI test result will be treated. STI syndromic management will only be provided for vulvovaginitis considered on clinical features due to candidiasis, for which additional treatment will be provided as per national guidelines (e.g. nystatin pessaries and/or clotrimazole cream)
^59^.

○ If the test result on any of the above assays is invalid, women will be asked to provide an additional self-collected swab and given further counselling on self-collection, to allow repeat testing on the same day in the clinic.

○ Residual fluid remaining in the GeneXpert sample processing tube will be retained for future laboratory testing with participants’ written consent.

○ Urinalysis will be conducted as per routine antenatal care (e.g. for protein and glucose) but residual urine will not be stored in intervention clusters.

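### STI prevalence is listed as a trigger for adjusted analyses, but the two arms measure it on different specimens, so an apparent imbalance can be a measurement artefact and the supplementary adjusted risk ratio can be biased

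*Protocol article*

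**What the plan says.** Statistical analysis puts the unadjusted comparison first: "Initial analyses will be unadjusted comparisons of intervention and control clusters". It then sets a condition for adjustment: "If there appear to be any important imbalances between randomised groups in terms of baseline demographic characteristics", continuing through risk factors for the birth outcomes to STI prevalence: "and the prevalence of specific STIs, adjusted analyses will be performed, and presented in addition to unadjusted comparisons".

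Enrolment visit procedures fix how STI status is obtained in each arm.

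- **Control clusters.** The routine procedures include "collection of a midstream urine specimen for urinalysis (protein and glucose testing". What is left over is kept: "Storage of residual urine specimen for off-site STI PCR testing to be conducted in batches". The section names all four infections, bacterial vaginosis (BV) included, as targets of this testing. It does not name the PCR platform.
- **Intervention clusters.** Women collect two vaginal swabs for same-day testing: "one swab will be tested for chlamydia, gonorrhoea and trichomonas using the GeneXpert platform" and "one swab will be tesed for bacterial vaginosis, using the BVBlue Test". The section adds that "residual urine will not be stored in intervention clusters". The only STI specimen material it keeps from this arm is leftover fluid from the GeneXpert sample tube, with consent.

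On accuracy, the Introduction describes laboratory nucleic acid amplification tests (NAATs) for chlamydia, gonorrhoea and trichomonas as highly accurate in urine and in genital swabs, and GeneXpert as equal to laboratory NAATs. For BVBlue it gives 90% sensitivity and 95% specificity. It gives no figure for PCR on urine for BV.

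**The concern.** A balance check assumes that a covariate means the same thing in both arms. Here the specimen, its handling and the timing of the test follow from the arm, so randomisation does not balance the measurement error. Two things can go wrong.

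1. **The trigger.** The arms can differ in measured prevalence when true prevalence is the same, and this can set off an adjusted analysis that nothing real calls for.
2. **The adjusted estimate.** If urine misses infections that a swab would find, the control women recorded as negative include some infected women at higher risk. The intervention women recorded as negative include fewer. Within that stratum the intervention looks protective even if it does nothing.

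At stake is the adjusted risk ratio reported beside the main one. Readers may prefer it precisely because an imbalance was reported.

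**Working it through.** The article gives no figure of its own on this point, so there is none to reproduce. The check asks what the planned rule would return when true prevalence is equal in both arms and treatment has no effect.

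**Inputs from the article**
- Prevalence in the pilot study (Introduction): chlamydia 19%, gonorrhoea 11%, trichomonas 38%, BV 18%, any of the four 54%.
- Relative risk for infection and outcome: 1.4. The article gives this for trichomonas and preterm birth; it is applied here to every infection and to the composite outcome.
- Outcome risk 18%, target relative reduction 23%, intra-cluster correlation 0.003 (Sample size).
- BVBlue sensitivity 90%, specificity 95%.

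**Assumptions**
- The pilot prevalences are the true ones.
- Urine sensitivity is 90%, 80% or 70% with specificity 100%, and the swab is perfect. These are not figures from the article.
- Adjustment is by individual-level stratification (Mantel–Haenszel).

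**Formulas.** Risk if uninfected r0 = 0.18 / (1 + p × (1.4 − 1)); risk if infected r1 = 1.4 × r0. Apparent control prevalence = p × s, where s is urine sensitivity.

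**One case in full: any infection, p = 0.54, s = 0.70**
- r0 = 0.18 / 1.216 = 0.1480; r1 = 0.2072.
- Apparent prevalence: intervention 54%, control 0.54 × 0.70 = 37.8%. The false gap is 16.2 points.
- Test-positive stratum: risk 0.2072 in both arms, ratio 1.
- Test-negative stratum: intervention risk 0.1480. In the control arm the stratum is 0.622 of women, of whom 0.162 are infected, so the risk is (0.162 × 0.2072 + 0.46 × 0.1480) / 0.622 = 0.1634. Ratio 0.906.
- Mantel–Haenszel numerator: 0.1119 × 0.378 / 0.918 + 0.0681 × 0.622 / 1.082 = 0.0461 + 0.0391 = 0.0852. Denominator: 0.0783 × 0.54 / 0.918 + 0.1017 × 0.46 / 1.082 = 0.0461 + 0.0432 = 0.0893. Risk ratio 0.954, where the truth is 1.

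**All cases under no effect**

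| Covariate | p | s = 0.90 | s = 0.70 |
|---|---|---|---|
| Gonorrhoea | 11% | 0.996 | 0.988 |
| BV | 18% | 0.993 | 0.981 |
| Chlamydia | 19% | 0.993 | 0.980 |
| Trichomonas | 38% | 0.987 | 0.964 |
| Any infection | 54% | 0.983 | 0.954 |

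For any infection at s = 0.80 the value is 0.968. Against the 23% target, the largest single-infection shift is 0.036 / 0.23 = 16%, and the largest composite shift is 0.046 / 0.23 = 20%.

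**BV with the article's BVBlue figures.** Apparent intervention prevalence is 0.18 × 0.90 + 0.82 × 0.05 = 20.3%. The control figure depends on the unknown accuracy of urine PCR:
- At 90%/95% it is also 20.3%; the gap is 0 and the adjusted risk ratio 1.000.
- At 80%/95% it is 18.5%; the gap is 1.8 points and the adjusted risk ratio 0.995.
- At 70%/98% it is 0.18 × 0.70 + 0.82 × 0.02 = 14.2%; the gap is 6.1 points and the adjusted risk ratio 0.982. With 2000 women per arm and a design effect of 1 + 199 × 0.003 = 1.597, z is 4.0. A gap of that kind would probably be called an important imbalance.

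**With a real effect.** If treatment cuts risk by 45% in women with BV, the unadjusted risk ratio is (0.82 + 0.18 × 1.4 × 0.55) / (0.82 + 0.18 × 1.4) = 0.894. A log-link regression adjusting for measured BV gives 0.892 to 0.901 as urine accuracy runs from 80%/95% down to 30%/99%. The shift is small and can go either way.

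**The case against.** The strongest reply is that the main result is safe. The unadjusted comparison comes first, and adjustment is conditional and shown in addition. That stands. A reader might infer that the trial's primary risk ratio is biased; the article does not support that.

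Second, a reader might infer that a false imbalance is certain. It is not. It rests on assumed urine accuracy and vanishes if accuracy is equal. For chlamydia, gonorrhoea and trichomonas the article speaks of high accuracy in both specimens, which weakens the concern there. It says nothing of the kind for BV.

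Third, a reader might infer that the assays differ for all four infections. Because the control PCR platform is not named, a different assay for chlamydia, gonorrhoea and trichomonas is not established. A different specimen is. For BV the test principle differs too: a sialidase test in one arm, PCR in the other.

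Fourth, a bias of a third of the target effect can be reached (0.923, or 0.077 / 0.23), but only with a relative risk of 1.8, which the article does not give, together with 70% sensitivity and the any-infection composite. The plan speaks of specific STIs. Adjusting for several at once could shift the estimate more than one alone, but that was not calculated.

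Finally, the article refers detail to a separate analysis plan and describes intention to treat at the cluster level, so individual-level stratification may not be the method used. This limits the figures. It does not repair a rule that the article itself states and that compares unlike measurements.

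**Conclusion.** The concern holds in a limited form. The article makes STI prevalence a trigger for adjusted analyses while fixing a different specimen in each arm, and a different test principle for BV, with no common specimen kept. An apparent imbalance can therefore be a product of measurement, and adjusting for it can bias the supplementary adjusted risk ratio, toward benefit if urine under-detects and treatment does nothing.

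At a relative risk of 1.4, a perfect swab and urine sensitivity of 90% to 70%, the adjusted risk ratio under no effect is 0.996 to 0.964 for single infections and 0.983 to 0.954 for any infection. The case is strongest for BV and weaker for the other three. This is a point that should be fixed; it does not threaten the primary analysis.

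**What to change.** Remove STI prevalence from the list of characteristics that are checked for balance and lead to adjustment, and do not use arm-specific STI results as covariates for any outcome. Report enrolment prevalence by arm descriptively, stating the difference in specimen and test.

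If a between-arm comparison or adjustment is still wanted, restrict it to results from a specimen and assay common to both arms, and say that only enrolment results count, because later prevalence is affected by treatment. Urine is already collected for urinalysis in intervention clusters, so the enrolment residue could be stored and run in the same batch assay. That costs storage and assays. It would also be incomplete: recruitment began in July 2017, and unstored urine from intervention women already enrolled cannot be recovered.

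Deletion costs one possible supplementary covariate and leaves the sample size unchanged.
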